## Protocol

### Selection of participants

A total number of 90 participants will be recruited for the study on the overlap between stress and alcohol. The Sweden population in 2019 (National Institute of Statistics of Sweden) is approximately 10 million, the population between 18 and 65 years old is less than 5 million
^
1
^. In order to have a significant sample and using one of the most common calculus
^
2
^ to calculate samples with 5M of population, error of 10% and a confidence level of 95 % the sample size must be at least 45 users. Here in this study, two age groups are selected as a result a portion of the population is dropped. The sample size for the test will be 100 users and a 10% more taking into account possible drop offs. However, for stress and alcohol test we are going have 45 subject each as
3 and
4 consider 20 to 30 subjects for statistical significance.

The selection will be made from a larger number of people who will be asked to fill out a questionnaire, and who will also be interviewed to establish their qualifications to be enrolled as participants. The related information sheet, consent form and questionnaire are provided as
*Extended data*
^
16
^.

Each recruited participant will be called to the test site on two occasions, once for stress-related tests and once for alcohol-related tests. The test subjects are divided into two age groups: young (18 – 25 years) and elderly (50 – 70 years) as these age groups have variation in the performance according to the recent research. Sametime, it was also observed that the age between 25 and 49 are often stable in their driving performance. Participants for the stress test will receive a gift card of worth 1500 SEK as gratification for successfully completing all stages of the test. For alcohol test participants the amount of gratification is 2000 SEK.
Table 2 and
Table 3 demonstrate the approximate number of participants from different age groups and road user types, respectively.

**Table 2. T2:** Number of subjects from different age groups.

Tests	Young adult	Elderly	Total
*Alcohol*	20	25	45
*Stress*	20	25	45
**Total**	40	50	90

**Table 3. T3:** Number of participants from different road user types.

Actors	Young adult	Elderly	Total
*Car drivers*	5	7	12
*Motorcyclists*	5	6	11
*Cyclists*	5	6	11
*Pedestrians*	5	6	11
**Total**	20	25	45

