Being the first investigation of its kind, this study is exploratory rather than confirmatory (i.e., a hypothesis test). Therefore, it is not meaningful to perform a statistical power analysis. The size of the study population has been established from the estimated division into age groups and other category divisions with the purpose of obtaining exploratory quantitative results.

Inclusion criteria for the participants are:

Age: young adults (18 – 24 years) and elderly (50 – 70 years)Gender: male or femaleDriving license: yes (for car drivers and motorcyclists) Health/medicine: none (i.e., participant shouldn’t have any health related problem e.g. diseases and not be taking any medication)Language: English or SwedishBody height: 160 – 210 cmBody weight: 60 – 150 kgAlcohol usage: 5 –15 glasses per month (applicable for alcohol test only)Stress tolerance: only subjects with standard or high scores in the Vienna test measuring stress tolerance and flexibility.

Exclusion criteria for participant selection are motion sickness, problems using VR goggles, stress intolerance, hearing or vision impairment, presence of chronic disease or serious allergies and any relation such as teacher and student or employer and employee among the participants and researchers. Habitual computer games players will be excluded if they are expected to be “immune” to simulated stressful situations.

Based on the study plan a press release named ‘
Smarter AI vehicles with the help of citizens in Västerås’ has been posted on the Mälardalen University website. In the press release there is a Google form link that the participants can fill in and an email address for direct contact if they wish to participate in the study.

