### Design and procedure

One test leader, [name] from MDH, will be assigned to the management of the stress-related tests and [name] from Senseair will be assigned to manage the alcohol-related tests. The detailed description of different test scenarios and procedures are described in the following sections.

**
*Stress test*.** The stress test will be performed as a within-participant design. To induce stress during this part while driving, the participants will be asked to perform other specific tasks where a continuous increase of cognitive load will be required. To keep cognitive loads increasing during the performance, two tasks relevant for the purpose have been selected: time pressure and social stress. During the scenarios, three levels of stress will be induced to the participants. These levels are numbered as 0, 1 and 2. Stress condition with level 0 will be considered as the baseline. Consequently, levels 1 and 2 will be considered as low and high stress, respectively. The low stress condition will include time pressure and the high stress condition will include time pressure and social pressure. Moreover, the participants will drive on three kinds of road (driving condition) and a limited number of events and hazards will occur, allowing study of the drivers’ risk perception and behaviour when coping with unexpected risky events under increased cognitive load conditions. For bicyclists there will be only two types of driving condition. From the total number of participants, approximately 12 will be taking part in this test and they will be divided into three groups to randomize the sequence of stress-eliciting factor insertion during driving or riding a motorcycle in the simulation. For cyclists there will be only two subject groups containing approximately 22 participants each. Description of scenarios and the randomized sequence of scenarios in simulators for different actors are given in the subsequent sections below.
Table 4 illustrates the sequence of induction of stress to participants for 32 minutes of simulator participation. The time for simulator usage will differ for different actor groups. For cyclists, scenario S0.3 and S1.3c will be replaced by similar scenarios defined below. The notations for different scenarios in
Table 4 are further defined in the subsequent sections for different actor groups.

**Table 4. T4:** Test order for the different actors for stress.

Time	4	4	4	4	4	4	4	4	Total

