DC – 1: City roadDC – 2: Country road

S1 – Time pressure

S1.0 – No time pressureS1.1 – Time pressure

S2 – Social pressure

S2.0 – No social pressureS2.1 – Social pressure

E – Unexpected risky events

E1 – unexpected risky events on city roadE1.a – Rush hour heavy trafficE1.b – Car cutting-in in front of the cycleE1.c – Diversion due to construction works

E2 – Unexpected risky events on country roadE2.a – Sudden entry of a car from the side roadE2.b – Car brushing while passing the bicycleE2.c – Low visibility due to dusk

*Pedestrian*

As the pedestrian simulator tends to easily cause fatigue and nausea, tests will be conducted for limited duration and will include breaks every 5 – 10 minutes. The experiments will be performed using an urban scenario with/without time and social pressure. Moreover, some particular conditions will be simulated while conducting the experiment.

S1 – Time pressure

S1.0 – No time pressureS1.1 – Time pressure

S2 – Social pressure

S2.0 – No social pressureS2.1 – Social pressure

C – Particular conditions

C1 – Construction on the sidewalk (requiring the pedestrian to perform a slalom)C2 – Crowded sidewalk (lots of people moving slowly on the sidewalk)C3 – Prolonged red light at the crosswalk (with road traffic)

Since the pedestrian simulator is the one more likely to cause discomfort, a short break time is reserved as per
Table 6.

**Table 6. T6:** Test order for pedestrians.

Time	2	1.5	1.5	3	15	2	1.5	1.5	3	Total
	S1.0 + S2.0 (BL)	S1.1 (LS)	S1.1 (LS) + C1	S1.1 (LS) + C2	Break	S1.0 + S2.0 (BL)	S1.1 + S2.1 (HS)	S1.1 + S2.1 (HS) + C2	S1.1 + S2.1 (HS) + C3	31 min

BL: baseline, LS: low stress, HS: high stress.

**
*Alcohol test*.** The influence of alcohol consumption on behaviour in the simulator models will be studied in each of the test subjects by first running a test in the sober condition, then consuming alcohol with 0.8 g alcohol/kg body mass. This will normally result in a breath alcohol concentration well above the US legal limit of 0.4 mg/L. A test at this intoxication level is performed in all simulators. Then the participant is allowed to rest until BrAC has declined to 0.3 mg/L, and the test procedure is repeated at this concentration level. The final test run is performed when the subject has reached below 0.1 mg/L. The decline is typically 0.08 ± 0.01 mg/L per hour
^
24

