A number of different physiological data will be collected; heart rate (HR), heart rate variability (HRV), blood volume pulse (BVP), electromyogram (EMG), galvanic skin response (GSR), EEG and electro-oculogram (EOG). For the alcohol test, one additional measurement on BrAC will also be measured. These data will be used to produce model that can give objective measurements of stress and alcohol presence, and as a basis for assessing risky behaviours of road users by corelating with data from the Vienna test and simulators.

**
*Schedule*.** The tentative time plan for each of the steps for experiments on effects of stress and alcohol on road users are outlined below in
Table 8.

**Table 8. T8:** Schedule of various parts of the experiment.

Date	Events
2020-06-01 –	Advertisement for volunteers for stress and alcohol tests
2020-09-16 – 2020-10-31	Information meeting, questionnaire and feedback session for stress and alcohol tests
2020-09-20 – 2020-11-15	Selection of volunteers and signing of consent forms for stress and alcohol tests
2020-10-16 – 2020-11-30	Cognitive assessment by Vienna test of volunteers for stress test
2020-12-01 – 2021-01-15	Cognitive assessment by Vienna test of volunteers for alcohol test
2021-01-15 – 2021-01-31	Pilot study for stress test
2021-02-01 – 2021-02-15	Pilot study for alcohol test
2021-02-16 – 2021-03-31	Main study for stress test with 45 participants
2021-02-20 – 2021-04-05	Self-confrontation interviews for stress test
2021-04-01 – 2021-05-31	Main study for alcohol test with 45 participants
2021-04-16 – 2021-05-15	Self-confrontation interviews for alcohol test
2021-04-16 – 2020-05-20	Miscellaneous tasks

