GDPR issues	Personal data management. Assignment of responsibility. Right of refusal. Right to terminate participation any time. Right to receive copy of stored personal data. Right to have stored personal data erased. Test person data collection, storage and management.
Code key holder	Mälardalen University (MDH)
Responsible person from MDH	[name]
Responsible person from Senseair	[name]

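### The stress-test gift card depends on finishing every stage, which gives an unwell or distressed participant a financial reason to continue; pay the simulator session in full once it has started

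*Protocol article*

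**What the plan says.** Under Selection of participants, the payment rule for the stress test reads: "Participants for the stress test will receive a gift card of worth 1500 SEK as gratification for successfully completing all stages of the test". The next sentence gives 2000 SEK for the alcohol test and attaches no completion condition.

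The stages are not listed. Table 8 gives separate windows to "Cognitive assessment by Vienna test of volunteers for stress test", the main simulator study and "Self-confrontation interviews for stress test".

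Under Design and procedure, participants in the stress test will "perform other specific tasks where a continuous increase of cognitive load will be required". Low stress is time pressure alone; high stress adds social pressure. For pedestrians the protocol foresees discomfort: "As the pedestrian simulator tends to easily cause fatigue and nausea, tests will be conducted for limited duration".

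On protection, Table 9 under Ethical issues lists "Right to terminate participation any time" and does not mention payment. The entry criteria admit "only subjects with standard or high scores in the Vienna test measuring stress tolerance and flexibility", and the protocol adds: "Exclusion criteria for participant selection are motion sickness, problems using VR goggles, stress intolerance".

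**The concern.** The person with the best reason to stop is the one who risks losing the card by stopping. The test is designed to put people under pressure, and the authors expect one of the four simulators to make some of them feel sick. A right to stop that may cost the whole payment is less free in practice than it reads on paper.

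The timing makes this sharper. By the simulator slot in Table 5, a participant has already been on site for two and a half hours (08:00 to 10:30, or 13:00 to 15:30). Table 9 names the gratification as one of two benefits to test subjects, so the document itself treats it as an incentive. What is at stake is participant protection, not the validity of any analysis.

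**Working it through.** No statistical figure in the plan needs reproducing. The check is a reading of the payment term, the timing of the stress blocks, and simple cost arithmetic.

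**1. Does stopping in the simulator fail the condition?** The undefined stages could mean the simulator sessions alone, or the Vienna assessment, the simulator and the interview together. On either reading the simulator run is included, so someone who stops during it has not met the stated condition.

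**2. Where do the high-stress blocks fall?**
- Table 4 (car drivers, motorcyclists and cyclists): 8 blocks × 4 min = 32 min. High stress is blocks 6 to 8: 3 × 4 = 12 min, and 12/32 = 37.5%.
- Table 6 (pedestrians): active time is 2 + 1.5 + 1.5 + 3 + 2 + 1.5 + 1.5 + 3 = 16 min, and with the 15-minute break 31 min, as the table states. High stress is the last three blocks: 1.5 + 1.5 + 3 = 6 min, and 6/16 = 37.5%.

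The 32 minutes is the Table 4 schedule; the text says simulator time varies by actor group. The 37.5% locates the high-stress time at the end of the run. It does not measure pressure to continue.

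**3. What would paying early stoppers cost?** The documents give no stop rate, so the rates below are assumptions. Each stopper costs at most 1500 SEK.

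| Assumed stop rate, all 45 | Expected stoppers | Cost at most |
|---|---|---|
| 5% | 45 × 0.05 = 2.25 | 3,375 SEK |
| 10% | 45 × 0.10 = 4.5 | 6,750 SEK |
| 20% | 45 × 0.20 = 9 | 13,500 SEK |

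Taking only the 11 pedestrians, assumed rates of 10%, 20% and 30% give at most 1,650, 3,300 and 4,950 SEK. The total for 45 people is at most 45 × 1500 = 67,500 SEK, which the present rule already pays if everyone finishes. That ceiling holds unless stoppers are replaced.

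**4. What does an early stop cost in data?** Table 3 has actor-by-age cells of 5 to 7 people. One person is 1/7 = 14% to 1/5 = 20% of a cell. A stop before block 6 removes that share of the cell's high-stress data; a later stop removes less.

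**The case against.** The strongest reply is that the harm rests on silence. The sentence says what earns the full card. It does not say that a person who stops receives nothing, and a reader who infers certain forfeiture goes beyond the text. Terms on withdrawal are often set out in the information sheet and consent form, which the article places in its extended data and which are not shown here. That limit stands. It does not remove the point, because the article does state a condition. If the sheet softens it, the article's sentence should be aligned with the sheet.

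A reader might also infer that the term contradicts the right to stop in Table 9. It does not: the right remains, and only its practical cost is in question.

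The protocol already lowers the risk. It screens out people prone to motion sickness, trouble with VR goggles or stress intolerance, requires an adequate Vienna score, limits pedestrian running time and includes a 15-minute break. Ethics approval is reported. All of this makes a stop less likely, but none of it changes what the written term puts at risk for a person who does need to stop.

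The objection with most substance concerns data. Full payment on an early stop removes the financial incentive to finish the high-stress blocks. Cells are small, and in the multi-user runs one person's exit affects the others. This cost is real and is counted below. It does not justify keeping an unwell person in the simulator.

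**Conclusion.** The point holds as a cheap improvement in participant protection. As written, payment of 1500 SEK depends on finishing, nothing shown preserves it for someone who stops, and the most demanding 37.5% of the scheduled run comes last. That this gives a distressed participant a reason to continue is an inference, but a direct one, since the authors themselves foresee fatigue and nausea.

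Three stronger readings are not supported:
- A reader might infer that results will be biased or that the sample size is affected. Nothing in the documents shows this, and no estimate or sample size changes.
- A reader might extend the point to the alcohol test. Its payment sentence carries no completion condition.
- A reader might want payment split across every stage, including the Vienna assessment. The Vienna stress-tolerance score is an entry criterion, so a Vienna share would also pay people who are screened out, and the protection sought does not need it.

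The conclusion assumes that the information sheet does not already give a part-payment rule. If it does, what remains is an alignment of wording.

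**What to change.** Change the payment sentence under Selection of participants along these lines: *A participant who starts the stress simulator session receives the payment for that session in full, even if they stop, or are stopped, early for any reason. Any share set aside for the later self-confrontation interview is paid on attendance.* No Vienna share and no fixed split is needed; the sponsor decides whether to reserve an interview share. Make the information sheet match, or bring the article into line with it if it already says this.

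Costs:
- **Money:** at most 1500 SEK per early stopper, within the 67,500 SEK ceiling for 45 participants unless stoppers are replaced.
- **Administration:** the study plan was part of the approved ethics application, so an amendment may be needed. People already enrolled should be told: Table 8 scheduled consent for 2020-09-20 to 2020-11-15, and Study status reports 43 people with cognitive tests done before November 2020.
- **Data:** possibly a few more missing high-stress blocks, each such stop costing up to 14–20% of a cell's high-stress data. Recording the time and reason of every stop would show how much is lost.

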### Platform

Simulators for the concerned tests will be provided by one of the SIMUSAFE partner institutions ITCL CENTRO TECNOLOGICO, Spain.
Figure 1 demonstrates the simulator for car drivers. It has three LCD displays for visualization of the frontal view with a horizontal field of view of 120 degrees, steering wheel and driver’s seat with proper safety measures. Simulators for motorcyclists and cyclists are depicted in
Figure 2 and
Figure 3, respectively. Participants for both motorbikes and cycles will have similar frontal views with LCD displays. Treadmill and VR accessories will be used to run the tests with pedestrians.
Figure 4 shows the experimental setup for pedestrians. There will be two simulators for each type of actor in the test premise. The simulators occupy approximately 10 m
^2^ of room area and can be positioned in almost any office or laboratory environment.

### Data/statistical analysis

The data analytics will comprise a data storage infrastructure to gather all relevant data (actor model states, user, cognitive and behavioural assessment data and annotations). This infrastructure will be integrated in IBM Bluemix cloud platform together with the Sensorization Platform, further processing will be performed in the Data Analysis Server.
IBM Streaming and Predictive Analytics from the platform will be employed to pre-filtering raw data sent to the Data Analysis server, for the real-time identification of events of interest and characteristic data patterns to be translated into components of the Actor Model. This data analysis to obtain required performance and isolate impacting factors will operate in three phases.

Phase 1 information fusion, data abstraction, and data pre-processing will be performed based on a combination of statistical, machine leaning (i.e. both supervised and unsupervised learning) and signal processing methods and techniques. Here, a robust and scalable data cleaning strategy will be established with domain-specific knowledge, including sub-processes like cleaning, filtering, sampling or/and normalization. Previous work on data pre-processing
^
17
^ using both structured and unstructured data will serve as basis for online automated data cleaning. Traditional feature extraction methods
^
18
^ will be adapted to handle scalability issues in the domain. Novel strategies to fuse data at feature level and at data level considering a defined fusion mechanism
^
19
^ will be used.

During Phase 2 data mining and knowledge discovery, a combination of potential sequences in the learning and search procedure will be investigated. The similarity assessment in the time series will be done by measuring the distance between probability distributions in the time series data mining
^
20
^. A combination of statistical model and fuzzy modelling algorithm will be applied to automatic addition/deletion of rules, as well as adjustment of the membership functions. A continuous learning procedure will be developed to keep the model constantly updated
^
21
^. New mining methods for the discovery of knowledge will be developed.

For Phase 3 learning, reasoning and model creation, adaptation of dynamic knowledge representation approaches will be achieved by combining different artificial intelligence
^
22
^ methods. This has a connection with Phase 2 as the data driven knowledge, rules and patterns will be considered as input. To provide decision support, hybrid approach will be applied using different traditional machine learning algorithms, such as case-based reasoning, and clustering
^
23
^.

So, in overall objective of this study, is to observe [separately] the effects of *Stress*(S) and *Alcohol-consumption*(A) on *driving performance*(P) (i.e., S-->P & A-->P). In the manipulation Stress (excluding pedestrians), we also control for different *Road conditions*(R) that may interfere with the observed effects (i.e., a confounding factor), and include *Situational Risk*(S) as an additional factor that has a potential of interacting with the main effects of stress and alcohol consumption (i.e., S*R*S-->P). b.t.w., this gives rise to the question of why not do the same also with alcohol consumption (i.e., A*R*S-->P). In realization of these, a set of observatory measures are included in the instantiation of each factor as described next chapters.

### Design and procedure

One test leader, [name] from MDH, will be assigned to the management of the stress-related tests and [name] from Senseair will be assigned to manage the alcohol-related tests. The detailed description of different test scenarios and procedures are described in the following sections.

**
*Stress test*.** The stress test will be performed as a within-participant design. To induce stress during this part while driving, the participants will be asked to perform other specific tasks where a continuous increase of cognitive load will be required. To keep cognitive loads increasing during the performance, two tasks relevant for the purpose have been selected: time pressure and social stress. During the scenarios, three levels of stress will be induced to the participants. These levels are numbered as 0, 1 and 2. Stress condition with level 0 will be considered as the baseline. Consequently, levels 1 and 2 will be considered as low and high stress, respectively. The low stress condition will include time pressure and the high stress condition will include time pressure and social pressure. Moreover, the participants will drive on three kinds of road (driving condition) and a limited number of events and hazards will occur, allowing study of the drivers’ risk perception and behaviour when coping with unexpected risky events under increased cognitive load conditions. For bicyclists there will be only two types of driving condition. From the total number of participants, approximately 12 will be taking part in this test and they will be divided into three groups to randomize the sequence of stress-eliciting factor insertion during driving or riding a motorcycle in the simulation. For cyclists there will be only two subject groups containing approximately 22 participants each. Description of scenarios and the randomized sequence of scenarios in simulators for different actors are given in the subsequent sections below.
Table 4 illustrates the sequence of induction of stress to participants for 32 minutes of simulator participation. The time for simulator usage will differ for different actor groups. For cyclists, scenario S0.3 and S1.3c will be replaced by similar scenarios defined below. The notations for different scenarios in
Table 4 are further defined in the subsequent sections for different actor groups.

**Table 4. T4:** Test order for the different actors for stress.

Time	4	4	4	4	4	4	4	4	Total
**SG – 1** **DC – 1**	S1.0 + S2.0 (BL)	S1.1 (LS)	S1.1 (LS) + E1.a	S1.1 (LS) + E1.b	S1.0 + S2.0 (BL)	S1.1 + S2.1 (HS)	S1.1 + S2.1 (HS) + E1.b	S1.1 + S2.1 (HS) + E1.c	**32** **mins**
**SG – 2** **DC – 2**	S1.0 + S2.0 (BL)	S1.1 (LS)	S1.1 (LS) + E2.a	S1.1 (LS) + E2.b	S1.0 + S2.0 (BL)	S1.1 + S2.1 (HS)	S1.1 + S2.1 (HS) + E2.b	S1.1 + S2.1 (HS) + E2.c	
**SG – 3** **DC – 3**	S1.0 + S2.0 (BL)	S1.1 (LS)	S1.1 (LS) + E3.a	S1.1 (LS) + E3.b	S1.0 + S2.0 (BL)	S1.1 + S2.1 (HS)	S1.1 + S2.1 (HS) + E3.b	S1.1 + S2.1 (HS) + E3.c	

SG: subject group, DC: driving condition, BL: baseline, LS: low stress, HS: high stress.

During the experiments, two participants from each actor group will be tested in the simulator each day. Each of the participants will be clearly briefed about the task and their responsibilities. Afterwards, physiological equipment will be attached to their body. Each participant will require around 2.5 hours to prepare fully for the tests. They will participate for about 40 minutes including some practice. After the test finishes, they will be debriefed, and the equipment will be removed.
Table 5 shows the time plan of a test day for participants (car drivers, motorcyclists and cyclists).

**Table 5. T5:** Schedule of a test day for participants in stress test.

Time	Test events

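### In every stress half of Table 4 the event-free stressed block precedes both event blocks, so a block-level event effect is aliased with time under the stressor

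*Protocol article*

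**What the plan says.** The Stress test part of Design and procedure says: "The stress test will be performed as a within-participant design". The secondary tasks are of a kind "where a continuous increase of cognitive load will be required", and the article continues: "To keep cognitive loads increasing during the performance, two tasks relevant for the purpose have been selected: time pressure and social stress". It then defines level 0 as baseline, level 1 as time pressure, and level 2 as time plus social pressure. Events are included to study behaviour "when coping with unexpected risky events under increased cognitive load conditions".

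On order, the article says of the participants that "they will be divided into three groups to randomize the sequence of stress-eliciting factor insertion during driving or riding a motorcycle in the simulation". Table 4 is presented as the "sequence of induction of stress to participants for 32 minutes of simulator participation". Each of its three rows has the same layout:

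- Low-stress half: baseline, LS, LS + event a, LS + event b.
- High-stress half: baseline, HS, HS + event b, HS + event c. In the first row, for example, the seventh block is "S1.1 + S2.1 (HS) + E1.b".

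Between rows only the road and its set of events change. Table 6 gives pedestrians the same pattern with their particular conditions.

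Data/statistical analysis brings in situational risk "as an additional factor that has a potential of interacting with the main effects of stress and alcohol consumption". The sentence that does so sets pedestrians aside.

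**The concern.** In a within-participant design, block order is the main threat to a comparison between blocks. Here nobody meets an event in the first stressed block of a half, and nobody has an event-free stressed block later in that half. Fatigue, practice or habituation under the stressor would therefore show up as an effect of the hazard. If such drift differed between low and high stress, it would show up as an interaction between stress and situational risk, which is one of the relations the article sets out to examine. Counterbalancing low and high stress, or running every event at both levels, would leave this problem in place, because it arises inside each half.

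**Working it through.** **The article's own totals.** Table 4: 8 × 4 = 32 min, as stated. Table 6: 2 + 1.5 + 1.5 + 3 + 15 + 2 + 1.5 + 1.5 + 3 = 31 min, as stated.

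**Layout of Table 4 (all three rows).** T counts the blocks already spent under the current stressor.

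| Block | 1 | 2 | 3 | 4 | 5 | 6 | 7 | 8 |
|---|---|---|---|---|---|---|---|---|
| Stress | BL | LS | LS | LS | BL | HS | HS | HS |
| Event | 0 | 0 | 1 | 1 | 0 | 0 | 1 | 1 |
| T | – | 0 | 1 | 2 | – | 0 | 1 | 2 |

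**Aliasing.** Event = [T = 1] + [T = 2] in every block of every row. A model with intercept, LS, HS, event and indicators for T = 1 and T = 2 has 6 columns and rank 5. Without the event column the rank is still 5. With an unrestricted time shape, the event effect is not estimable from block means.

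**Size of the shift.** Block centres since stressor onset are 2 min (no event) and 6 and 10 min (event). The gap is (6 + 10)/2 − 2 = 6 min. If the true event effect is zero and performance drifts by g per block, the contrast returns (1 + 2)/2 × g − 0 = 1.5g.

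**Interaction.** With drifts gL and gH in the two halves, the interaction pooled over both event blocks carries 1.5(gH − gL). This is zero when the drifts are equal.

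**Price of assuming a drift shape.** The figures are variances of the event effect in units of the block residual variance, for one run of Table 4.

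- No time term: (1 + 1/2)/2 = 0.75.
- Linear T: within halves, the sums of squares are 4/3 for event and 4 for T, with cross-product 2. Residual: 4/3 − 2²/4 = 1/3, so the variance is 3.0, or 3.0/0.75 = 4.0 times larger. The event–T correlation is 2/√(4/3 × 4) = 0.87.
- One linear trend over all eight blocks: variance 1.0, or 1.0/0.75 = 1.33 times larger.

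**Scale, as illustration only.** The article gives no drift. Assume g between −0.2 and +0.2, in SDs of the paired difference. The bias then lies between −0.30 and +0.30. The 95% half-width of a mean paired difference, t(0.975, n − 1)/√n, is 0.35 for n = 12 + 11 + 11 = 34, 0.64 for n = 12 and 0.67 for n = 11 (Table 3 counts).

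**Pedestrians (Table 6).** Centres are 0.75 min against (2.25 + 4.5)/2 = 3.375 min, a gap of about 2.6 min.

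**After rotation.** Put the event-free block first, in the middle or last, with T running over 0, 1 and 2. The drift entering the contrast is then 1.5g, 0 and −1.5g, which averages to 0 with equal numbers. The model above has rank 6 of 6, and the event–T correlation is 0.

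**The case against.** **A rising load within each half is not shown.** A reader might infer from the wording on increasing load that later blocks are more loaded by design. The article explains the increase as steps from baseline to low to high stress. Within a half Table 4 applies the same stressor throughout, and a baseline block separates the halves. This stands: drift within a half is a possibility of unknown size and sign, not something the plan sets.

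**Not inseparable in every sense.** This also stands. The aliasing is exact only for block means with a free time shape. Block 6 is event-free and follows the low-stress hazards, which is why a single session trend costs little. The article plans identification of events and time-series methods, samples simulator data at 250 Hz and records physiology continuously. Event-locked comparison inside a block is thus open for a sudden hazard such as a pedestrian crossing. It helps less for heavy traffic or fog, and the article does not describe it as the contrast to be used.

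**The question may concern the same event at two stress levels.** Research question i can be read that way, and situational risk is not defined as event minus no-event block means. But event b, the only one run at both levels, has T = 2 under low stress and T = 1 under high stress. With equal drift, high minus low for event b carries g − 2g = −g. That shift is tied to stress level, so it does not free the event effect either.

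**Exploratory status and a sensible order.** Establishing the stressor before the hazard is defensible given the stated purpose. The exploratory label explains the missing power analysis, but it does not make an aliased contrast interpretable.

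**Pedestrians.** They are excluded where situational risk is introduced, so Table 6 is secondary and 34, not 45, is the relevant number.

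**Conclusion.** The concern holds for block-level event versus no-event contrasts in car drivers, motorcyclists and cyclists, about 34 people. The layout, not the sample size, causes it: event blocks sit 6 minutes later under the stressor in every row, and 1.5 blocks' worth of any drift is counted as event effect. The groups described as randomising the sequence do not vary it. The pooled stress-by-event interaction is biased only if drift differs between low and high stress.

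The documents do not support saying that the event effect can never be recovered or that results will be biased by a known amount. Recovery is possible under a linear drift at the variance cost shown, or in part by event-locked analysis. In the illustration even the largest assumed bias stays below the half-width at n = 34. The problem is therefore one of interpretation that is worth removing while the order can still be changed.

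**What to change.** Rotate the event-free block over the three stressed positions within each half, and include block position in the within-person analysis.

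- Assign the three orders as nearly equally as possible within road-user type, and within age group where numbers allow. Exact thirds are impossible in the Table 3 cells of 5 and 7. In a cell of 5 split 2, 2, 1 the residual drift is at most 1.5g × (2 − 1)/5 = 0.3g, which the position term can take up.
- Assign orders within each road, not by subject group. Table 4 ties group to road, so assigning by group would alias order with road.

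The cost is three order files per simulator and one model term. There are two downsides: some participants meet a hazard directly after the stressor starts, and a later event-free block may carry arousal from the preceding hazard.

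If the order must stay, state that block-level event versus no-event differences include time under stress, and report event-locked comparisons for the sudden hazards. Either way, the description of the groups as randomising the sequence should be brought into line with Table 4.
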